### 2.13. Sample Size Calculation

To calculate the effect size, we used a preceding RCT on acupuncture therapy for MD with DHI assessment, as there have been no clinical studies for GJD effectiveness in chronic dizziness [58]. The null hypothesis is that *μ*_GJD_ = *μ*_placebo_, while the alternative hypothesis is *μ*_GJD_ ≠ *μ*_placebo_, where *μ* denotes the mean difference of DHI score between the baseline and endpoint. With the mean difference (−3.63) and the standard deviation (4.84), under the assumption of correlation coefficient (0.1), the sample size was calculated as 29 per group (two-sided, *α* = 0.05 and 1 − *β* = 0.8). Therefore, we are going to recruit 78 participants for both groups (39 per group) under a 25% anticipated dropout rate.

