### 2.14. Statistical Analysis

The primary and secondary variables for the effect assessments will be statistically analyzed by analysis of covariance (ANCOVA) or rank ANCOVA with group and site as covariates. If any demographic characteristics show significant difference between groups, those variables will also be used as covariates. When there is a significant interaction between diagnosis (MD, psychogenic dizziness, or dizziness of unknown cause) and group, subgroup analysis will be performed.

The confidence interval (CI) of BI will be addressed and blinding will be deemed successful when the CI includes the zero value. For safety assessment, the chi-squared test or Fisher's exact test will be performed with the proportions of AEs, while lab results will be compared between groups by chi-squared test (proportions of abnormal results) or McNemar's test (before-and-after comparison within a group). An independent statistician ([name]) will analyze any data with a significance level of 0.05 (two-sided) with SAS 9.4 software (SAS Institute Inc.).

The primary analysis will be performed with the full analysis set, which is defined as the group of participants who were prescribed at least once or more the GJD or placebo pills and for whom DHI was evaluated more than once. The missing data will be imputed with the last observation carried forward method. The per protocol set will be additionally analyzed, which includes only the participants who complete all the scheduled visits. We are going to include any participants who took at least one pill of the study drugs for the safety assessment.

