## 3. Results and Discussion

This study is a prospective, multicenter, randomized, double-blind, placebo-controlled, parallel-group, clinical trial to explore the effectiveness, safety, and cost-effectiveness of a herbal drug, GJD, for patients with chronic dizziness attributable to MD, psychogenic dizziness, or dizziness of unknown cause. We are going to administer to patients GJD or placebo pills for 8 weeks and follow them up for 12 months. Four TKM hospitals in Korea will enroll 78 participants.

Dizziness may ensue from a variety of central or peripheral diseases and in some cases as a drug complication. This may complicate the diagnostic process. This study will include patients diagnosed with MD, psychogenic dizziness, or dizziness of unknown cause, which may create an issue with homogeneity. However, there were previous clinical studies which also focused on the symptom of dizziness with varied origin to demonstrate new efficacy [28, 35], including an acupuncture study for chronic dizziness [24], which has meaningfully been referred for this trial.

GJD is a widely prescribed herbal pill in Korea, but it is mostly used for patients with severe deficiency pattern/syndrome, especially those complaining of marked fatigue [14, 21]. However, based on the seminal work* Dongeuibogam* [10], we expect GJD to also manage chronic dizziness.

This RCT included various diseases (MD, psychogenic dizziness, or dizziness of unknown cause) inducing dizziness, which might reduce the level of homogeneity of patient population. The investigators discussed this issue, which might affect significantly the study results in the future. However, it was taken into consideration that this trial should reflex the real clinical practices as much as possible, which means that GJD is a herbal drug and it has been described based on pattern/syndrome identification in TKM. So, we think the screening process is one of the key parts for this trial to include eligible participants. Investigators and coordinators should be trained with written standard operating procedures for the trial before enrolling the first participants, since this study is a multicenter trial, to control the high quality throughout the whole process. Also, an independent monitor will regularly visit all the hospitals for auditing ethical and scientific issues.

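### Demographics enter the primary and secondary ANCOVA only if they differ significantly between arms, so chance rather than prognosis sets the adjustment; the covariates should be named in advance

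*Protocol article*

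**What the plan says.** Protocol article, section 2.14, analyses the primary and secondary variables by "analysis of covariance (ANCOVA) or rank ANCOVA with group and site as covariates". It then makes further adjustment conditional on the data: "If any demographic characteristics show significant difference between groups, those variables will also be used as covariates". The statistician "will analyze any data with a significance level of 0.05 (two-sided"), so the screening level is taken here as 0.05. The article gives no number of candidate demographics.

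Diagnosis appears in section 2.14 only as a possible effect modifier: "When there is a significant interaction between diagnosis (MD, psychogenic dizziness, or dizziness of unknown cause) and group, subgroup analysis will be performed".

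Section 2.7 describes blocked randomisation stratified by study site, with the allocation list held only by the statistician and the manufacturer. Diagnosis is not a stratum. Section 3 nevertheless says of the mix of Meniere's disease, psychogenic dizziness and dizziness of unknown cause that it is something "which might reduce the level of homogeneity of patient population", and accepts that this may bear on the results.

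**The concern.** A baseline significance test in a randomised trial tests a null hypothesis known to be true. Its result says nothing about whether the variable predicts DHI, and prediction is the reason to adjust. A strongly prognostic variable is left out about 95% of the time, and an irrelevant one comes in about 5% of the time. The fitted model therefore depends on which chance imbalances occur, and the precision that prognostic covariates offer is mostly not obtained.

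Diagnosis shows the problem best. It is the factor that the authors single out, yet nothing puts it in the model. As a clinical rather than a demographic variable, it may not even be screened under the rule.

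A second, separate matter is that the diagnosis-specific analysis is tied to an interaction test with little power at this sample size.

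**Working it through.** **1. The plan's own figure.** Section 2.13 states: "With the mean difference (−3.63) and the standard deviation (4.84), under the assumption of correlation coefficient (0.1"), and "the sample size was calculated as 29 per group (two-sided, *α* = 0.05 and 1 − *β* = 0.8"). Taking 4.84 as the SD of the change score, the normal approximation is n = 2 × (1.960 + 0.842)² × (4.84/3.63)² = 2 × 7.85 × 1.778 = 27.9, so 28. The exact t-test calculation gives 29 (power 0.801). With 25% dropout, 29/0.75 = 38.7, so 39 per arm and 78 in all, as in "recruit 78 participants for both groups (39 per group) under a 25% anticipated dropout rate". The figure reproduces, and this point does not alter it.

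**2. How often the rule changes the model.** For k independent candidates tested at 0.05, P(at least one enters) = 1 − 0.95^k. This is 14% for k = 3, 23% for 5, 34% for 8 and 40% for 10. The value of k is an assumption.

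**3. Precision.** Simulation at 39 per arm with 5 independent candidates, one of them having correlation r with the outcome (both assumed). Standard errors of the group difference are in SD units:

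| r | Rule | Always adjusted | Excess |
|---|---|---|---|
| 0.1 | 0.229 | 0.227 | 1% |
| 0.3 | 0.227 | 0.218 | 4% |
| 0.6 | 0.220 | 0.183 | 20% |

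A closed form supports this and supplies r = 0.5. When the prognostic variable is not selected, its standardised imbalance is truncated at ±1.96, so the variance of that imbalance falls from 1 to 1 − 2 × 1.96 × 0.0584/0.95 = 0.759. The variance of the estimate, relative to no truncation, is then (1 − r²) + 0.759r², against 1 − r² with adjustment.
- r = 0.3: √(0.978/0.910) = 1.04
- r = 0.5: √(0.940/0.750) = 1.12
- r = 0.6: √(0.913/0.640) = 1.19, close to the simulated 20%

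**4. Type I error.** The same truncation makes the test slightly conservative, because the fitted model usually assumes variance 1 when the true value is smaller. At r = 0.5 the size is 2 × [1 − Φ(1.96/√0.940)] = 2 × [1 − Φ(2.02)] = 0.043; simulation gave about 0.044. It was about 0.042 at r = 0.6, 0.035 to 0.037 at r = 0.7, and 0.05 within simulation error at r of 0.1 and 0.2.

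**5. Power at 29 per group**, planned effect 3.63/4.84 = 0.75 SD, for r = 0.3 / 0.5 / 0.7:
- prespecified adjustment: 0.83 / 0.89 / 0.97
- selection rule: 0.79 / 0.80 / 0.81
- no adjustment: 0.80 / 0.81 / 0.80

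**6. Interaction test (secondary).** Assume three equal diagnosis groups with the 3.63-point effect in one and none in the others. The mean effect is 1.21, and the sum of squared deviations is 2.42² + 2 × 1.21² = 8.785. Divided by 4.84² = 23.43, this is 0.375. The noncentrality is (m/2) × 0.375, where m is the number per arm per diagnosis.
- 78 patients, m = 13: noncentrality 2.44, power 26%
- 58 patients, m = 9.67: noncentrality 1.81, power 20%

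With an unequal 20/30/50 split, or the effect in two groups instead of one, power runs from 15% to 29%. With effects of 7.26 / 3.63 / 0 it is 48% to 66%.

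Half-width of a within-diagnosis 95% CI: 1.99 × 4.84 × √(2/13) = 3.8 points with 78 patients; 2.01 × 4.84 × √(2/9.67) = 4.4 with 58.

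**The case against.** The rule is mechanical and uses baseline data only. Group and site are fixed. Once candidates are listed, nobody chooses a covariate after looking at outcomes, and an article may properly leave that list to the full protocol or analysis plan. The precision loss depends on an assumed correlation; few demographics may predict DHI strongly, and at r = 0.1 the loss is 1%. The rule is also no worse than not adjusting: at r = 0.6 the unadjusted standard error is 0.228 against 0.220 under the rule. Deleting the sentence alone therefore gains nothing; the gain comes from prespecifying prognostic covariates. All of this stands. It limits the size of the point but does not rescue the rule, which a faithful analysis plan would inherit.

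Four stronger readings are tempting and are not supported:
- **Inflated false positives.** A reader might infer this from data-driven selection. The calculations show a size at or slightly below 5%.
- **The interaction test unfixes the primary analysis.** It triggers a subgroup analysis and does not touch the primary model. Testing interaction before subgroups is also common practice.
- **Diagnosis-specific results will be suppressed about three times in four.** That is a single assumed scenario with all 78 patients evaluable, and section 2.14 does not forbid descriptive results when the test is not significant.
- **Baseline DHI is left out of the model.** It is not named, but a condensed article using ANCOVA may take it as understood.

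**Conclusion.** The point holds in limited form. Section 2.14 states a covariate rule that selects on chance imbalance, leaves the adjusted model unsettled until the arms are compared, and recovers almost none of the precision that prespecified adjustment would give. The excess standard error ranges from about 1% to 20% across assumed correlations of 0.1 to 0.6; the upper figure needs a strong predictor and should not be quoted alone. The number of candidates, their independence and the correlations are all assumptions. The article's only correlation, 0.1 in section 2.13, is not said to relate a covariate to the outcome.

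The absence of diagnosis from both the strata and the named covariates sits poorly with the article's own account of heterogeneity. The weak interaction test is a secondary reporting matter. A change should be made, but the validity of the primary test is not threatened.

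**What to change.** Delete the sentence that adds demographics on the basis of baseline significance tests. Name the covariates in advance for the primary and secondary models: baseline DHI (for a secondary scale, its own baseline value), site and diagnosis.

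The cost is wording plus about three degrees of freedom: one for the baseline score and two for diagnosis, since site is already in the model. With 58 evaluable patients and four sites, residual degrees of freedom go from 58 − 5 = 53 to 50. The sample size stays at 29 evaluable per group and 78 in all.

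Separately, report the group difference with its 95% CI within each diagnosis, together with the interaction p-value, whatever that p-value is, and label these results descriptive. The cost is three wide intervals, about ±3.8 points with 78 patients or ±4.4 with 58. Both are wider than the planned 3.63-point effect, so they cannot support claims for a single diagnosis.

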#### 2.12.3. Blinding Assessment

This is a double-blind clinical trial with placebo control. Both study participants and TKM doctors will remain blind until the end of the trial. At the end of treatment of each participant, they will be asked in which group they think they belonged to, the GJD group, placebo group, or unknown, and the new Blinding Index (BI) will be calculated following [56]. The index score varies within 1 (complete lack of blinding), 0 (consistent with perfect blinding), or −1 (guessed they were in the opposite group).

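### Blinding is deemed successful whenever the Blinding Index CI includes zero, so modest to moderate unblinding often passes with 29 to 39 patients per arm

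*Protocol article*

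**What the plan says.** Section 2.12.3 (Blinding Assessment) sets the timing, "At the end of treatment of each participant", and the question: "they will be asked in which group they think they belonged to, the GJD group, placebo group, or unknown". Table 1 shows the new BI at V6 only. The scale is described as follows: "The index score varies within 1 (complete lack of blinding), 0 (consistent with perfect blinding), or −1 (guessed they were in the opposite group". Section 2.14 (Statistical Analysis) then gives the decision rule: "The confidence interval (CI) of BI will be addressed and blinding will be deemed successful when the CI includes the zero value".

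The article does not say whether the index is calculated per arm or pooled. It sets no limit on how far the CI may extend from zero and does not say how two arm-level indices would be combined. No level is given for this CI, but the general rule is that the statistician "will analyze any data with a significance level of 0.05 (two-sided", so 95% is assumed below.

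**The concern.** A CI that includes zero shows only that the data do not exclude BI = 0. With few patients the CI is wide and may also include values that represent real unblinding. The rule still returns 'successful', and does so more readily the less information there is. Because guesses are collected only at V6, each dropout before V6 loosens the test further.

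The rule may also err the other way. If the index is calculated per arm and most patients in both arms believe they had the active pill, one index is positive and the other negative. Both CIs can exclude zero although the guesses do not distinguish the arms.

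The primary outcome, DHI, is patient-rated, as are most secondary scales, and the blind depends on a placebo matched for look, taste and smell. Readers will use the stated blinding verdict when they judge a positive DHI result.

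**Working it through.** **Arm sizes.** Section 2.13 gives "With the mean difference (−3.63) and the standard deviation (4.84), under the assumption of correlation coefficient (0.1" and concludes that "the sample size was calculated as 29 per group (two-sided, *α* = 0.05 and 1 − *β* = 0.8". Normal approximation: 2 × (1.960 + 0.842)² × (4.84/3.63)² = 27.9, so 28. With the noncentral t, 29 per group gives power 0.801. Dropout: 29/0.75 = 38.7, so 39, which agrees with "we are going to recruit 78 participants for both groups (39 per group) under a 25% anticipated dropout rate". The stated sizes reproduce. BI is therefore evaluated at n = 29 (after the expected dropout) and n = 39 (no dropout).

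**Formulas.** For one arm, BI = p_correct − p_wrong and Var(BI) = (p_correct + p_wrong − BI²)/n, with CI = BI ± 1.96 × SE. The share answering 'unknown' (u) is not in the document. It is an assumption, varied from 0 to 40%.

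**Largest observed BI that still passes.** Setting BI = 1.96 × SE gives BI² = (1 − u)/(n/3.84 + 1).
- u = 0: √(1/11.15) = 0.30 at n = 39; √(1/8.55) = 0.34 at n = 29.
- u = 40%: √(0.6/11.15) = 0.23 at n = 39; √(0.6/8.55) = 0.26 at n = 29.

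**Probability that the CI includes zero**, by exact multinomial enumeration:

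| Reading | True BI | u = 0 | u = 20% | u = 40% |
|---|---|---|---|---|
| One arm, n = 29 / 39 | 0.2 | 0.78 / 0.75 | 0.74 / 0.68 | 0.68 / 0.59 |
| One arm, n = 29 / 39 | 0.3 | 0.59 / 0.51 | 0.50 / 0.40 | 0.38 / 0.25 |
| One arm, n = 29 / 39 | 0.5 | 0.17 / 0.09 | 0.08 / 0.03 | 0.01 / 0.001 |
| Both arms must pass, n = 29 / 39 | 0.2 | 0.61 / 0.56 | 0.54 / 0.47 | 0.46 / 0.34 |
| Both arms must pass, n = 29 / 39 | 0.3 | 0.35 / 0.26 | 0.25 / 0.16 | 0.15 / 0.06 |
| Pooled, n = 58 / 78 | 0.2 | 0.67 / 0.56 | 0.58 / 0.47 | 0.47 / 0.35 |
| Pooled, n = 58 / 78 | 0.3 | 0.37 / 0.22 | 0.25 / 0.13 | 0.12 / 0.05 |

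With u = 0, a BI of 0.2 means 60% correct guesses and 0.3 means 65%.

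**Dependence on sample size alone.** At true BI 0.3 and u = 0, the one-arm pass probability is 0.59 at n = 29 and 0.51 at n = 39. It would be 0.125 at n = 100 and 0.008 at n = 200. The degree of blinding is the same in all four.

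**Both arms guess GJD alike (per-arm index only).** If 70% in each arm guess GJD and u = 0, the true BIs are +0.40 and −0.40. At n = 39 the half-width is 1.96 × √((1 − 0.16)/39) = 0.29, so at the expected values the CIs are 0.11 to 0.69 and the mirror image. Both CIs include zero with probability 0.13 (n = 29) or 0.07 (n = 39), so the rule fails this trial 87 to 93% of the time. At 75% GJD guesses it fails 97 to 99%, and at 60% it fails 39 to 44%. With a pooled index the 70% case passes about 96 to 97% of the time, so the problem does not arise.

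**Reference case.** With guesses split 50/50 and u = 0, requiring both arms to pass fails a perfectly blinded trial 10 to 12% of the time.

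**The case against.** Several points on the other side stand.
- One-arm pass rates with no 'unknown' answers are the least favourable case for the rule. If both arms must pass, or if many patients answer 'unknown', the miss rate falls: at BI 0.3 with n = 39, from 0.51 (one arm, u = 0) to 0.26 (both arms, u = 0) or 0.25 (one arm, u = 40%). The figures must be shown as a range.
- A reader might infer that the rule lets gross unblinding through. It does not: at BI 0.5 one arm passes at most 0.17 of the time.
- A reader might infer that the rule certainly fails a well-blinded trial whose patients all hope for GJD. That needs a per-arm index. A scale on which −1 means opposite guessing suggests one, but neither section says so, and under pooling the problem disappears.
- A reader might suppose that the pill has a strong smell or taste that makes unblinding likely. The article says only that the placebo will be similar in appearance, taste and odor.
- The verdict governs no analysis set, model or imputation, and the CI is to be addressed in any case, so its width may be visible to readers.
- Guesses at the end of treatment may reflect perceived benefit, so a positive BI in the GJD arm need not mean the blind was broken. This limits any replacement statistic as well.

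Whether the index is per arm or pooled may be settled in a plan that is not shown. That does not rescue the stated rule: reading non-significance as success is wrong under either choice, and at BI 0.2 even the pooled index passes 0.35 to 0.67 of the time.

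**Conclusion.** The point holds in a limited form. The rule is stated without qualification and takes absence of evidence of unblinding as evidence of blinding. For modest to moderate unblinding it often gives the wrong answer at this sample size: over 0 to 40% 'unknown' answers, one arm passes with probability 0.59 to 0.78 at BI 0.2 and 0.25 to 0.59 at BI 0.3. Failing a trial in which both arms favour GJD is a second fault, but only if the index is calculated per arm.

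These figures assume a Wald 95% CI, the variance formula above, and 29 to 39 guesses per arm. It would go too far to conclude that the primary result is compromised: the fault lies in the blinding verdict alone. It should be corrected because that verdict will colour how a patient-rated primary outcome is read.

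**What to change.** Delete the pass/fail sentence in section 2.14. State that BI will be reported with its 95% CI for each arm, together with the between-arm difference in the proportion guessing GJD and its CI. Say that the arms will be read together and that end-of-treatment guesses can reflect perceived benefit.

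Do not use the sum of the two indices as if it were that difference. With G the proportion guessing GJD and u the proportion answering 'unknown', BI_GJD = 2G_GJD + u_GJD − 1 and BI_placebo = 1 − u_placebo − 2G_placebo. The sum is therefore 2(G_GJD − G_placebo) + (u_GJD − u_placebo), which is twice the difference when nobody answers 'unknown'. For example, 75% against 25% guessing GJD gives a difference of 0.5 and a sum of 1.0.

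If a verdict is wanted, compare the CI with a margin set in advance on the same scale, and allow 'inconclusive'. With CI half-widths at BI = 0 of 0.31 to 0.36 per arm (u = 0) or 0.24 to 0.28 (u = 40%), arms of this size cannot show that BI is close to zero, so 'inconclusive' is a likely outcome.

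The cost is wording only. The sponsor gives up an easy claim of successful blinding.

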## Abstract

This study protocol aims to explore the effectiveness, safety, and cost-effectiveness of a herbal medication,* Gongjindan* (GJD), in patients with chronic dizziness. This will be a prospective, multicenter, randomized, double-blind, placebo-controlled, parallel-group, clinical trial. Seventy-eight patients diagnosed with Meniere's disease, psychogenic dizziness, or dizziness of unknown cause will be randomized and allocated to either a GJD or a placebo group in a 1 : 1 ratio. Participants will be orally given 3.75 g GJD or placebo in pill form once a day for 56 days. The primary outcome measure will be the Dizziness Handicap Inventory score. Secondary outcome measures will be as follows: severity (mean vertigo scale and visual analogue scale) and frequency of dizziness, balance function (Berg Balance Scale), fatigue (Fatigue Severity Scale) and deficiency pattern/syndrome (qi blood yin yang-deficiency questionnaire) levels, and depression (Korean version of Beck's Depression Inventory) and anxiety (State-Trait Anxiety Inventory) levels. To assess safety, adverse events, including laboratory test results, will be monitored. Further, the incremental cost-effectiveness ratio will be calculated based on quality-adjusted life years (from the EuroQoL five dimensions' questionnaire) and medical expenses. Data will be statistically analyzed at a significance level of 0.05 (two-sided). This trial is registered with ClinicalTrials.gov NCT03219515, in July 2017.

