### 2.1. Objectives and Hypothesis

The primary objective of this study is to evaluate the effect of GJD administration for 8 weeks, compared to placebo, on chronic dizziness (MD, psychogenic dizziness, or dizziness of unknown cause). The alternative hypothesis is that the mean difference between Dizziness Handicap Inventory (DHI) scores at baseline and endpoint in the GJD group will not be equal to that in the placebo group.

Additionally, the changes in dizziness severity and frequency will be evaluated with validated scales. Further, the levels of fatigue, depression, anxiety, and quality of life (QoL) will be compared between the two groups posttreatment. The safety of GJD administration will be examined based on laboratory tests and adverse events (AEs). Finally, the cost-effectiveness of GJD will be evaluated with quality-adjusted life years (QALY).

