#### 2.12.4. Safety Assessment

The AEs will be monitored during the whole treatment period. The following adverse reactions are expected: anorexia, discomfort feeling of stomach area, nausea, vomiting, diarrhea, or rash on skins. The intensity and frequency of each episode will be recorded. Moreover, laboratory tests will be performed at baseline and the endpoint. Complete blood cell tests (red blood cell, hemoglobin, hematocrit, platelet, and white blood cell), serum biochemical tests (creatinine, BUN, ALT, AST, and glucose), and urinalysis (pH, specific gravity, glucose, ketone, red blood cell, nitrate, total protein, bilirubin, urobilinogen, and white blood cell) will be performed. If serious AEs occur, postmanagement will be properly conducted.

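### The laboratory tests named in section 2.14 cannot register worsening in a participant whose value is already abnormal at entry, and entry admits liver and kidney values up to 3 times the upper limit

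*Protocol article*

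**What the plan says.** The objectives in section 2.1 give laboratory results and adverse events as the two bases for safety: "The safety of GJD administration will be examined based on laboratory tests and adverse events (AEs"). Section 2.12.4 says that "laboratory tests will be performed at baseline and the endpoint", and its chemistry panel is given as "serum biochemical tests (creatinine, BUN, ALT, AST, and glucose"). Table 1 places the two draws at V1 (screening) and V6 (day 56).

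The laboratory analysis is one clause of section 2.14: "lab results will be compared between groups by chi-squared test (proportions of abnormal results) or McNemar's test (before-and-after comparison within a group"). The same section handles adverse events separately: "the chi-squared test or Fisher's exact test will be performed with the proportions of AEs". The safety population is "any participants who took at least one pill of the study drugs for the safety assessment", and testing is done "with a significance level of 0.05 (two-sided").

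The exclusion criteria in section 2.5 remove a patient for AST, ALT, BUN or creatinine only when the value exceeds 3 times the upper limit of normal. All four analytes are also in the safety chemistry panel.

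**The concern.** The entry rule and the analysis rule do not fit together. The entry rule knowingly admits people with liver or kidney values above normal. The analysis then reduces each value to one of two categories, so anyone who starts in the abnormal category has no higher category to move to. A rise in ALT from 2.9 to 9 times the limit is scored the same as no change.

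Safety is a stated objective, and section 2.9 justifies the placebo control by the lack of earlier clinical trials of GJD pills against placebo. The trial collects the numerical values needed to see such a rise, and the two named tests then discard that information. A report of no difference in laboratory abnormalities could be read as more reassuring than the method allows.

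**Working it through.** **Inputs.** The planned tests come from section 2.14, the entry limit of 3 times the upper limit from section 2.5, and the draws at V1 and V6 from Table 1. Section 2.13 gives 39 per group recruited and 29 per group after 25% dropout. The article gives no sample size or power for laboratory safety.

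**The plan's own figure.** A two-sample t-test with a difference of 3.63, an SD of 4.84, two-sided 0.05 and 80% power needs 28.90, rounded up to 29 per group. Then 29/0.75 = 38.7, rounded up to 39 per group, or 78 in total. This agrees with section 2.13. It serves here only to supply the denominators 39 and 29.

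**Why the tests cannot see the rise.** Take abnormal to mean outside the reference range.
- McNemar's test uses only the discordant pairs (normal to abnormal, and abnormal to normal). A participant abnormal at V1 and V6 is concordant and drops out of the statistic.
- The chi-squared test at V6 counts that participant as abnormal, exactly as it counts someone whose value has not moved.

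**Illustration.** Suppose k of 39 per arm enter between 1 and 3 times the limit on one analyte. All k in the GJD arm rise above 3 times the limit, none in the placebo arm do, and nobody else changes category.
- Planned chi-squared test: k/39 against k/39 abnormal at V6, so the statistic is 0 and p = 1.00.
- Planned McNemar's test in the GJD arm: 0 discordant pairs, p = 1.00.
- Worsening counted directly: k/39 against 0/39. With equal arms of n, the two-sided Fisher p-value is 2 × C(n, k) / C(2n, k).

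| k per arm | Planned chi-squared | Planned McNemar | Fisher on worsening, 39 per arm |
|---|---|---|---|
| 2 | 1.00 | 1.00 | 2 × 741/3,003 = 0.49 |
| 4 | 1.00 | 1.00 | 2 × 82,251/1,426,425 = 0.12 |
| 6 | 1.00 | 1.00 | 0.025 |
| 8 | 1.00 | 1.00 | 0.005 |

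With 29 per arm and k = 6, the same formula gives 2 × 475,020/40,475,358 = 0.023.

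**How many are affected.** The documents give no share of participants abnormal at entry, so 5–20% is an assumption.
- Of 39 recruited per arm: 0.05 × 39 = 1.95 and 0.20 × 39 = 7.8, or about 2 to 8.
- Of 29 per arm still present for the V6 draw: 0.05 × 29 = 1.45 and 0.20 × 29 = 5.8, or about 1.5 to 6.

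**The case against.** The strongest reply is that safety does not rest on these two tests. Section 2.1 names adverse events as well, the abstract says "To assess safety, adverse events, including laboratory test results, will be monitored", section 2.12.4 records the intensity of events, and section 2.14 compares event proportions between arms. A large rise in ALT could be reported and compared by that route. This stands, and it limits the point to the laboratory tests. It does not remove the point, because the article states no rule for when a laboratory change becomes an adverse event.

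Second, the article does not define abnormal. If the full protocol uses a clinical-significance judgement or a higher multiple of the limit, some worsening would change category. This also stands as a condition on the conclusion. The missing definition is not itself a fault in an article; the point is the binary method that the article does state.

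Third, the numbers are small. Even in the extreme illustration, two or four worsened participants against none give Fisher p-values of 0.49 and 0.12. That is correct. Much of the gain would lie in seeing and describing the worsening rather than in a significant test.

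Two further readings are tempting but not supported:
- A reader might infer that a chance excess of abnormal entrants in one arm would produce a false difference at V6. Under randomisation, the type I error of the between-group test already covers that chance imbalance. Adjusting for baseline adds precision but is not needed for validity.
- A reader might infer that an abnormality first found in the V6 sample could not be recorded, because adverse event collection ends there. Table 1 marks both laboratory tests and adverse events at V6, so the finding can be entered against that visit.

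McNemar's test makes no comparison with placebo, but the plan labels it as within-group and supplies the chi-squared test for the between-group question.

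**Conclusion.** The point holds for the laboratory tests stated in section 2.14. On the ordinary reading of abnormal, they give no weight to worsening in anyone abnormal at both V1 and V6, whatever its size. A reader might go further and say that the safety objective as a whole cannot see such worsening. The documents do not support that, because adverse events are a second, separately tested route, though not an assured one for laboratory changes.

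The conclusion rests on two assumptions: that abnormal means outside the reference range, and that some participants enter between 1 and 3 times the limit. The counts of about 2–8 of 39, or 1.5–6 of 29, rest on the assumed 5–20% and could be lower. The primary efficacy analysis is not affected. This is a weakness in a stated safety analysis that wording can correct.

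**What to change.** Keep the entry criterion, the scheduled draws and the binary tests. Add to section 2.14, and carry into the analysis plan:

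1. A between-arm comparison of V1-to-V6 change in each continuous laboratory value, adjusted for the V1 value, by ANCOVA or rank ANCOVA (the methods already named for the efficacy variables).
2. Baseline-to-V6 shift tables by arm.
3. A between-arm comparison of treatment-emergent worsening, defined as a new abnormality in those normal at V1 or a rise from V1 of a size fixed in advance in those already abnormal. The definition should be set before unblinding.

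The cost is a few sentences, slightly more analysis, and more exploratory safety comparisons, which should be labelled as such and read descriptively. No extra samples, visits or participants are needed.
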